### Ethical Considerations

The study received an approval certificate from the BC Cancer Agency, Interior Health Authority, and Thompson Rivers University Research Ethics Board (H22-03105/27-04-2023/27-04-2024). Research team members completed the Tri-Council Policy Statement: Ethical Conduct for Research Involving Humans, a course on research ethics. Participants will receive a gift voucher for their time and efforts at baseline and after 3 months.

### Quality, Safety, and Monitoring

The research assistants developed a master sheet, which includes the study location and site; participant codes (study ID); follow-up tracking; the participant’s name and contact information (email, phone number, and address); the randomization arm; date and time and modules completed; and whether the intervention is in progress or incomplete. Research assistants reminded participants via email and phone to review intervention module information. Discussions among the research team addressed any adverse effects that could result from study participation, the validity and integrity of the data, the enrollment rate relative to expectations, participant characteristics, retention, adherence to the protocol (potential or real deviations), and data completeness. We have established a data and safety monitoring plan to ensure participants’ safety. These activities are reviewed by screening results and other available data at weekly research meetings among the principal investigator, the research team, and other relevant research team members; in a quarterly review of data safety and enrollment by the research team, including the principal investigator, research assistants, and relevant research team members; and in an annual review by the ethics board.

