## Methods

### Research Design

This study uses implementation science through an open-cohort randomized controlled trial (RCT) involving an intervention and a control group. Implementation science is defined as the promotion of the systematic uptake of research findings and other evidence-based practices into routine practice to improve the quality and effectiveness of health services [33,34]. An RCT is a study in which participants are randomly allocated to receive a new treatment (experimental group), a standard treatment (comparison group), or no treatment at all (placebo group) [35]. This RCT is a single-center, parallel-group study with stratified block randomization that follows the CONSORT (Consolidated Standards of Reporting Trials) guidelines (Checklist 1) and assesses a cancer navigation intervention provided by professional navigators.

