### Recruitment and Data Collection

Recruitment for the study took place with permission from local groups, institutions, and establishments. The recruitment call was distributed through printed posters, social media, community networks, and online advertisements. During the initial recruitment conversation, the research assistant described the study project, informing participants of what is expected, reading the study information sheet, and providing clarification. Participants were screened for eligibility and randomized into the study. Participants who met the criteria were enrolled via a web link or QR code.

Participants who provided informed consent were randomized (1:1) into one of the two study groups: the intervention group received the cancer navigation intervention and the control group received the SOC (the usual medical care offered by health care practitioners; Figure 1). The computer-based randomization balanced random assignments to the two groups in blocks of 5 participants. The baseline study time point spanned January 2025 to March 2025, the 3-month follow-up spanned April 2025 to June 2025, and the 6-month follow-up spanned July 2025 to September 2025.

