### Sample Size and Power

The study is sufficiently powered to detect a clinically meaningful difference while accounting for the longitudinal design. For effect size, the power assumption calculation was based on a minimum clinically significant difference of 7 points on the FACT-B [41]. An estimated SD of 16.93 was used, derived from existing literature on adult survivors of cancer. An attrition rate of 25% was estimated based on the potential for dropout during the 6-month follow-up schedule. While the study is a single-center RCT, the randomization is balanced using blocks of 5 to mitigate potential clustering effects and ensure equal distribution across the 2 arms. With a 5% level of significance (2 tailed) and 90% power, the required sample size was calculated as 108 participants. The total recruitment target is set to 150 participants (75 in the intervention group and 75 in the control group).

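### Recruiting staff hold the list of past arms in an open trial with one stated block size of 5, so allocation was partly predictable; check for selection before claiming effectiveness

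*Protocol article*

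**What the plan says.** Four statements in the protocol article bear on this point.

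- **Who recruits** (Recruitment and Data Collection): "During the initial recruitment conversation, the research assistant described the study project, informing participants of what is expected".
- **Who holds the arms** (Quality, Safety, and Monitoring): "The research assistants developed a master sheet, which includes the study location and site; participant codes (study ID); follow-up tracking". The listed contents continue with names and contact details, and then "the randomization arm; date and time and modules completed; and whether the intervention is in progress or incomplete". Research assistants also remind participants about intervention modules, so they work with assignments day to day.
- **How allocation is made** (Recruitment and Data Collection): "The computer-based randomization balanced random assignments to the two groups in blocks of 5 participants". Sample Size and Power repeats the block size as a benefit: "the randomization is balanced using blocks of 5 to mitigate potential clustering effects and ensure equal distribution across the 2 arms". No other block size appears. Research Design adds "This RCT is a single-center, parallel-group study with stratified block randomization", without naming the factors.
- **Order of events** (Recruitment and Data Collection): one paragraph reads "Participants were screened for eligibility and randomized into the study. Participants who met the criteria were enrolled via a web link or QR code", and the next reads "Participants who provided informed consent were randomized (1:1) into one of the two study groups".

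The control group receives usual care and, in Table 2, no sessions.

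**The concern.** A computer-generated sequence conceals the next assignment only if it cannot be inferred from the earlier ones. Here the earlier arms sit on a sheet kept by the role that talks to prospective participants, the arms cannot be mistaken for one another, and the block size is fixed. Someone with all of that in view has a better-than-even guess of the next arm, and sometimes knows it, before deciding how to present the study, when to book the person or how to read a borderline eligibility answer.

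What is at stake is the comparability of the arms. FACT-B, the primary measure, is self-reported. If people with a better outlook were drawn, even unintentionally, towards navigation, a difference could appear that navigation did not cause.

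**Working it through.** **Inputs.** Block size 5 and 1:1 allocation (Recruitment and Data Collection); 164 randomised, 82 per arm (Study Timeline); 7-point target difference on FACT-B (Sample Size and Power). The article gives no figure for predictability, so there is none to reproduce.

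**Assumptions.** A block of 5 cannot be split evenly, so each block is taken as 3:2 or 2:3 at random. The recruiter sees all earlier arms, knows the block size and knows where blocks begin.

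**Step 1: enumerate a block.** There are C(5,3) + C(5,2) = 10 + 10 = 20 equally likely sequences. At each position the best guess is the more likely arm given the earlier ones.

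| Position | Best guess right | Known with certainty |
|---|---|---|
| 1 | 10/20 = 50% | 0 |
| 2 | 12/20 = 60% | 0 |
| 3 | 12/20 = 60% | 0 |
| 4 | 14/20 = 70% | 2/20 = 10% |
| 5 | 14/20 = 70% | 8/20 = 40% |
| Mean | 62% | 10% |

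At position 4, certainty arises only after three identical arms. At position 5 it arises after a 3:1 run. Over the trial, 0.10 x 164 = 16.4 assignments. Without sight of past arms the figures are 50% and 0%.

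**Step 2: a known split.** If the recruiter knew which arm had three places, the figures would rise to 72% right and 30% certain (0.30 x 164 = 49.2). A constant 3:2 split is ruled out: it would give 0.6 x 164 = 98 against 66, not 82 and 82. A strictly alternating split fits 1:1, but nothing in the article suggests one.

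**Step 3: is the block size the cause?** In a simulation of 164 assignments in randomly mixed blocks of 4, 6 and 8, always guessing the arm that lags gave about 68% correct. That is more than 62%. Varying the block size does not help while past arms are visible; the open arm list is what matters.

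**Step 4: from guessing to bias.** Suppose every enrolment were steered, with favoured and disfavoured enrolees differing by s points. With a share g of guesses right, the arms differ by s x (2g - 1). For g = 0.62 the multiplier is 2 x 0.62 - 1 = 0.24.

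- If s is a difference in stable FACT-B level, the shift 0.24s is present at baseline and at 6 months. The Data Analysis section compares changes from baseline, and 0.24s - 0.24s = 0.
- If s is a difference in expected change, the shift stays in the comparison. The article gives no value for s. For assumed values of 3.5 and 7 it would be 0.84 and 1.68 points, against the 7-point target. These show scale only and are not estimates.

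**The case against.** The strongest reply is that the key link is not stated. The article says research assistants developed a sheet containing the arm. It does not say that the individuals who recruited looked at it during enrolment, or that they knew the block size. Stratification means a recruiter would have to follow each stratum separately. Much of the eligibility information comes from participants themselves, who came through posters, social media and online advertisements and enrolled by web link or QR code. Detail on concealment may sit in the full protocol. All of this stands as a limit on the size of the problem. It does not remove it, because the article goes beyond silence: it places the arm list with the recruiting role.

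Three stronger readings are tempting, and the documents do not support them.

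- **That people were enrolled after their arm was known.** The wording that puts randomization before enrolment invites this. The next paragraph, however, says those who consented were randomized, and Table 1 puts consent and the baseline survey at first contact. Table 2 lists baseline surveys in a post-allocation column, so the order needs clarifying, but no breach is shown.
- **That steering occurred.** Rural residence was 44/54 in the intervention group and 30/54 in the control group. These are completers after the loss of 56 of 164 (34%), so differential dropout or chance could explain the gap.
- **That the result is biased by a stated number of points.** Differences of about 0.8 to 3.1 points can be generated with assumed s of 3.5 to 7 and g of 0.62 to 0.72. They are differences in level, which the change-from-baseline analysis would largely remove if the steered trait is stable, and the values of s have no source in the documents.

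**Conclusion.** The point holds as a stated vulnerability, not as evidence of a biased result. With past arms visible and blocks of 5 split randomly 3:2 or 2:3, up to about 62% of assignments could be guessed and about 10% known. Both figures assume a recruiter who sees every earlier arm and can follow the blocks; unnamed stratification factors and the possibility that different individuals did the two tasks would lower them. The size of any bias cannot be derived from the documents. Steering on a stable FACT-B level would largely cancel in the planned comparison; steering on expected change or outlook would pass through it undetected. That is enough to require a check before the time-by-group result is read as an effect of navigation.

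**What to change.** All 164 participants are randomised and data collection closed on 30 September 2025, so access and block settings can no longer be repaired for them. For this trial:

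1. From the existing allocation log, compute each participant's within-block probability of the intervention given earlier assignments in the same stratum, using the actual rule for splitting blocks of 5. Test its association with baseline FACT-B and with 6-month FACT-B within arm (Berger-Exner check). The baseline test can use all those randomised with a baseline score; the 6-month test can use only the 108 completers, so a null result there is weak reassurance.
2. Fit the main FACT-B comparison with baseline FACT-B as a covariate. This is mainly for precision and chance imbalance and does not cure steering.
3. State whether staff who recruited or screened could see the arm column during enrolment and whether they knew the block size. If they could see arms, limit the effectiveness conclusion accordingly. Also clarify the order of consent, eligibility, baseline survey and randomization.

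For any further enrolment, close the arm column to staff who recruit or screen, and have the computer system release each assignment only after consent, eligibility and baseline data are locked. Varying the block size without closing the list is not a remedy.

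The cost is one extra sensitivity analysis on data the trial should already hold, a short statement of who had access, and possibly a more cautious conclusion. No patients or visits are added.

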### Data Analysis

All quantitative data will be analyzed using the intention-to-treat principle. Participants who engaged with the study from October 2025 to December 2025 will be included in the analysis.

The FACT-B is the primary measure used to evaluate the effectiveness of professional navigation on health-related QOL. Changes in FACT-B total scores and the scores on its 5 subscales (physical, social, emotional, and functional well-being and the breast cancer subscale) from baseline (T1) to 3 months (T2) and 6 months (T3) will be compared between the cancer navigation intervention and SOC control groups. A repeated-measure ANOVA will be used to determine the interaction between time and the treatment group. A change of 6 to 7 points on the FACT-B is considered clinically significant for this population.

Financial toxicity is an indicator of socioeconomic distress. Financial burden will be quantified using the COST-FACIT instrument. Descriptive statistics will be generated. To determine the impact of financial toxicity on health-related QOL, ANOVAs will be conducted to assess the associations between COST-FACIT scores and health-related QOL outcomes.

The BCNS analyzes participant satisfaction across 13 items to evaluate the user-friendliness and clarity of the program objectives.

The PSNS uses 26 items to measure overall satisfaction with the navigation process. Higher scores will be correlated with secondary outcomes such as treatment adherence using predictive validity testing.

The Satisfaction With Interpersonal Relationships Survey evaluates soft skills and trust in the professional navigator. Discriminant validity will be assessed by distinguishing between technical competence and interpersonal satisfaction scores.

Qualitative data from the Breast Cancer Navigation Interview will be analyzed using the thematic analysis approach by Braun and Clarke [42] to identify barriers to and facilitators of the adoption of professional navigation. These qualitative findings will be synthesized with the quantitative results to explain the how and why behind the intervention and effectiveness data. Two independent researchers will read the transcripts multiple times to achieve immersion. Participant quotations will be analyzed in terms of the content; what was being discussed; context; language use, such as metaphors, symbols, repetitions, and pauses; and initial interpretative comments by the participants [43]. Researchers will look at associations among emerging themes and group them according to conceptual similarities; track them; log them; and then extract major themes, subthemes, and relevant excerpts from the interview transcripts. Codes will be generated to capture emerging concepts and grouped into clusters based on conceptual similarities to categorize themes.

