## Results

### Study Timeline

Data collection took place from January 2 to September 30, 2025. Funding was secured in June 2022; the study has progressed through data validation and cleaning; publication of the results is anticipated in December 2026. A total of 164 participants were recruited at baseline and randomized into either the intervention group (n=82) or the control group (n=82), as shown in Figure 1. At the end of the 6-month follow-up, 108 participants had completed the study (54 in the intervention group and 54 in the control group), resulting in a response rate of 65.85%.

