### Sociodemographic Characteristics

In the intervention group (n=54), the largest age group was 40-49 years (17/54, 31.48%), whereas the control group (n=54) was slightly older, with the largest age group being 50-59 years (24/54, 44.44%). Educational attainment was comparable across both groups, with individuals who had completed college, associate, or technical levels comprising 33.33% (18/54) of the intervention group and 37.04% (20/54) in the control group.

Differences were observed in employment and residency. The control group reported a higher employment rate (25/54, 46.3%) than the intervention group (16/54, 29.63%). A higher percentage of the intervention group resided in rural areas (44/54, 81.48%) compared to the control group (30/54, 55.56%).

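### The analysis set is defined by engagement in a window that opens after data collection closed, contrary to intention to treat; separately, the stated ANOVA would keep only participants with complete visits unless missing scores are handled

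*Protocol article*

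**What the plan says.** The Data Analysis section opens with the principle: "All quantitative data will be analyzed using the intention-to-treat principle". The next sentence gives an inclusion rule: "Participants who engaged with the study from October 2025 to December 2025 will be included in the analysis". For the primary measure, FACT-B, the same section plans comparisons of change from T1 to T2 and T3 and states: "A repeated-measure ANOVA will be used to determine the interaction between time and the treatment group". It describes no handling of missing scores.

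On dates, Study Timeline says: "Data collection took place from January 2 to September 30, 2025". Recruitment and Data Collection agrees: "the 6-month follow-up spanned July 2025 to September 2025".

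On numbers, Study Timeline reports: "A total of 164 participants were recruited at baseline and randomized into either the intervention group (n=82) or the control group (n=82"). It then reports that at the end of follow-up "108 participants had completed the study (54 in the intervention group and 54 in the control group), resulting in a response rate of 65.85" per cent. Sample Size and Power had allowed for 25% attrition. Sociodemographic Characteristics uses the completers as the denominator: "In the intervention group (n=54), the largest age group was 40-49 years", with 54 likewise for control.

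**The concern.** There are two problems, and they should be kept apart.

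The first is the inclusion sentence. Intention to treat fixes the analysis set at randomisation. A rule that admits people according to what they did months later replaces that set with one that the intervention itself may have shaped: navigator calls and reminders are a plausible reason to remain engaged. The dates make it worse, because no scheduled visit falls in the window.

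The second is the analysis method. Even with that sentence removed, a classical repeated-measures ANOVA needs a score at every visit from every participant. With a third of those randomised not completing follow-up, an analysis described as intention to treat could in practice be an analysis of those who stayed. The estimate would then describe a selected subgroup, and the randomised comparison would no longer protect it.

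**Working it through.** **Dates side by side**

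| Item | Period | Section |
|---|---|---|
| Data collection | 2 January to 30 September 2025 | Study Timeline; Abstract |
| 6-month follow-up | July to September 2025 | Recruitment and Data Collection |
| Engagement window for inclusion | October to December 2025 | Data Analysis |

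The window starts on 1 October, one day after collection closed, so it overlaps no data-collection visit. Three readings are possible:

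- Literal: nobody qualifies through a study visit, so no usable analysis set results.
- Loose (people still engaged at the end): selection after randomisation, contrary to the preceding sentence.
- Period of analysis: compatible with intention to treat, but not what the sentence says.

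**Attrition** (inputs from Study Timeline; planned rate from Sample Size and Power)

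- The article's own figure reproduces: 108 / 164 = 65.85%.
- Non-completers: 164 − 108 = 56, and 56 / 164 = 34.1%.
- Per arm: 82 − 54 = 28, and 28 / 82 = 34.1% in each.
- At the planned 25%, losses among 164 would have been 0.25 × 164 = 41, so the actual loss is 15 higher.

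These 56 are people who did not complete follow-up. The date window did not produce that number.

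**What the loss could do to the estimate.** The split is the same in both arms (54 completers, 28 non-completers), so the difference between arms among all randomised is

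(108 × difference in completers + 56 × difference in non-completers) / 164.

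Suppose the completers show the article's 7-point clinically significant difference. The difference among non-completers is an assumption, since the article gives no data on it:

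| Assumed difference in non-completers | Difference in all 164 |
|---|---|
| 0 | (756 + 0) / 164 = 4.6 |
| 3 | (756 + 168) / 164 = 5.6 |
| 5 | (756 + 280) / 164 = 6.3 |
| 7 | (756 + 392) / 164 = 7.0 |
| 10 | (756 + 560) / 164 = 8.0 |

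The table shows only that the answer depends on people whose outcomes are missing. No row is a prediction, and a mixed model under missing at random would not be expected to return the first row.

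**Comparability of those described.** Rural residence is 44/54 (81.5%) against 30/54 (55.6%), Fisher exact p about 0.007. The article also reports an association of residence with COST-FACIT scores. Whether the imbalance arose at randomisation or through dropout cannot be told, because the characteristics of all 82 and 82 are not given.

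**The case against.** The inclusion sentence may simply be a drafting slip for the months in which the analysis was done. That would fit a data set closed on 30 September and then cleaned, and on that reading no one is selected. This is plausible, but it needs the sentence rewritten, so it softens the motive and leaves the fix unchanged.

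On the ANOVA, the objection is stronger. The article never says completers only and does not rule out imputation. A condensed article may leave missing-data handling to an analysis plan that is not shown, so silence on it is not in itself an error. Table 2 lists FACT-B at baseline and 6 months only. With two visits the time-by-group test amounts to comparing change scores, which is a standard analysis. The FACT-B and COST-FACIT results give no denominators, so nothing shown proves that the primary comparison used 108. Table 2 also lists the sociodemographic survey at later visits, which might explain the 54s. All of this stands, and it makes the second problem conditional.

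Losses were equal (28 and 28), the 108 completers match the stated required sample size, and the Discussion concedes that attrition could affect the analysis. Equal counts do not show that the same kinds of people left each arm, and reaching 108 answers a question about precision, not about bias. Still, no differential dropout has been demonstrated.

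A reader might infer that the engagement window and the ANOVA together exclude 56 participants. The article does not support that. The 56 are follow-up losses, and the window read literally would exclude everyone.

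**Conclusion.** The first problem holds as written and must be corrected: the rule for who is analysed contradicts both the declared principle and the study's own calendar. This rests only on the article's text.

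The second holds conditionally. If the repeated-measures ANOVA is run in its classical form without imputation, it will omit participants with missing visits. That would be at least the 56 non-completers (34.1%) if each lacks the 6-month score, and the result would not be the declared intention-to-treat analysis. The 54-per-arm denominators point that way without proving it.

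It would go too far to say that the reported FACT-B comparison is biased, or that the true effect is 4.6 points. The first would need the denominators and the characteristics of those lost. The second is one end of a range of assumptions about people with no reported outcome.

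**What to change.** 1. Delete the October to December sentence, or reword it as the period of analysis if that is what it means. State that all 164 randomised participants are analysed in the arm assigned, 82 vs 82.

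2. State a primary analysis that keeps every randomised participant with any FACT-B score: a likelihood-based mixed model or, if only T1 and T3 scores exist, multiple imputation from baseline FACT-B, residence, employment and age. Where non-completers have only a baseline score, a mixed model alone recovers little outcome information, so the imputation variables matter. If an existing analysis plan already provides for this, cite it and give the number analysed with each result.

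3. Add a missing-not-at-random sensitivity analysis for the 56 (delta-adjusted or reference-based) over a stated range, in both directions.

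4. Report baseline characteristics for 82 vs 82, with completers shown separately.

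Cost: wording and modest analysis work, with no new data. The confidence interval may widen. Between-arm FACT-B results already appear in the article, so any change of primary method must be labelled as made after outcome data were available, with the ANOVA specified in the article reported alongside.
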